## Abstract

**Background:**

The ability to walk is commonly reported as a top rehabilitation priority for individuals after a stroke. However, not all individuals with stroke are able to practice walking, especially those who require more assistance from their therapist to do so. Powered robotic exoskeletons are a new generation of robotic-assisted gait training devices, designed to assist lower extremity movement to allow repetitious overground walking practice. To date, minimal research has been conducted on the use of an exoskeleton for gait rehabilitation after stroke. The following research protocol aims to evaluate the efficacy and acceptability, and thus adoptability, of an exoskeleton-based gait rehabilitation program for individuals with stroke.

**Methods:**

This research protocol describes a prospective, multi-center, mixed-methods study comprised of a randomized controlled trial and a nested qualitative study. Forty adults with subacute stroke will be recruited from three inpatient rehabilitation hospitals and randomized to receive either the exoskeleton-based gait rehabilitation program or usual physical therapy care. The primary outcome measure is the Functional Ambulation Category at post-intervention, and secondary outcomes include motor recovery, functional mobility, cognitive, and quality-of-life measures. Outcome data will be collected at baseline, post-intervention, and at 6 months. The qualitative component will explore the experience and acceptability of using a powered robotic exoskeleton for stroke rehabilitation from the point of view of individuals with stroke and physical therapists. Semi-structured interviews will be conducted with participants who receive the exoskeleton intervention, and with the therapists who provide the intervention. Qualitative data will be analyzed using interpretive description.

**Discussion:**

This study will be the first mixed-methods study examining the adoptability of exoskeleton-based rehabilitation for individuals with stroke. It will provide valuable information regarding the efficacy of exoskeleton-based training for walking recovery and will shed light on how physical therapists and patients with stroke perceive the device. The findings will help guide the integration of robotic exoskeletons into clinical practice.

**Trial registration:**

NCT02995265 (clinicaltrials.gov), Registered 16 December 2016.

## Background

Stroke is a leading cause of adult disability, often resulting in hemiparesis, altered sensation, incoordination, cognitive changes, and speech disturbances [1, 2]. With improved detection and medical treatment of stroke, the prevalence of individuals living with such effects of stroke is continually increasing at the national and global scale [2–4]. A major factor associated with long-term disability after stroke is the ability to walk independently [5–8], and is often cited as a goal by individuals with stroke [9, 10]. However, nearly half of individuals with stroke do not regain the ability to walk independently, even after rehabilitation [11, 12]. It is thus important to develop rehabilitation strategies that will promote walking recovery after stroke.

Current best practice guidelines recommend that individuals with stroke should engage in early rehabilitative training that is intensive, repetitive, and task-specific to improve mobility and walking [13, 14]. However, it can be challenging to reach this guideline for individuals with more severe stroke; the amount of walking practice achieved during rehabilitation is especially low for individuals requiring more assistance from their therapist to stand and walk [15]. Electromechanical devices such as body weight-supported treadmills and treadmill-based robotic devices have been proposed to provide walking practice to non-ambulatory individuals during stroke rehabilitation [16, 17], though some research has not supported their use [18, 19]. A possible reason for the mixed findings is the suggestion that treadmill-based assisted gait training does not fully replicate the task-specificity of overground walking [20].

Powered robotic exoskeletons are a more recent technology developed to enable walking for anyone with lower extremity weakness, without the constraints of prior mechanical devices. These wearable robots strap around the torso and legs to control joint motion to automate overground walking and can be used independent of a treadmill or overhead harness system. Early research has demonstrated safe use of powered robotic exoskeletons for individuals with stroke, but few clinical trials have been conducted to determine the efficacy of using such devices; fewer still have compared exoskeletal gait training to standard physical therapy care during early stroke recovery and rehabilitation [21–23]. Additionally, no studies have yet explored the perception and experience of either individuals with stroke or physical therapists towards using powered robotic exoskeleton technology for rehabilitation, a necessary consideration when introducing technology into practice [24].

The present study is designed to examine the adoptability of a powered robotic exoskeleton for stroke rehabilitation by determining the efficacy and acceptability of exoskeleton-based gait retraining. More specifically, this mixed-methods trial aims to: 1) determine the efficacy of exoskeleton-based gait rehabilitation to improve walking ability, function, cognition, and quality of life; as well as 2) explore the experience and perception of using a powered robotic exoskeleton for rehabilitation from the perspective of patients with stroke and their physical therapists. It is hypothesized that exoskeleton-based gait rehabilitation will result in greater improvements in walking ability, function, cognition, and quality of life compared to usual physical therapy care.

## Methods

This nested mixed-methods study will be comprised of a multi-center, parallel-group randomized, controlled trial (RCT) with an embedded qualitative study [25]. A flow diagram of the study procedures can be seen in Fig. 1. The methods for the quantitative and qualitative components are described here separately.

**Fig. 1 Fig1:**
[figure not shown]
Flow diagram of mixed-methods study

### Quantitative component: randomized, controlled trial

#### Setting

The RCT will be conducted at three rehabilitation hospitals, GF Strong Rehabilitation Centre (Vancouver, Canada), Glenrose Rehabilitation Hospital (Edmonton, Canada), and Parkwood Institute (London, Canada). Participants will be recruited from each respective inpatient stroke rehabilitation units over a period of up to three years.

#### Participants

Consecutive patients with subacute stroke admitted at each rehabilitation hospital will be identified by their treating physiatrists and therapists to be screened for eligibility by a member of the research team. Individuals will be included if they: 1) are within 3 months of stroke onset (ischemic infarct or intracerebral hemorrhage); 2) have one-sided hemiparesis; 3) are 19 years of age or older; 4) are able to understand and follow directions in English; 5) are able to communicate (verbal or physical yes/no indication); 6) are cleared to participate in physical therapy; and 7) require significant assistance (maximal assistance from one or two people) to walk. Individuals will be excluded from the study if they have: 1) a significant musculoskeletal or other neurological condition; 2) cardiovascular contraindications to exercise; 3) co-morbidities that would preclude activity; 4) or pain which is intolerably worsened with exercise. Individuals will also be excluded if they have any contraindications to using the robotic exoskeleton (pregnant, height/weight restrictions). The site coordinator at each hospital with obtain informed consent from potential trial participants.

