#### Randomization

Participants will be randomized by the site coordinator after the baseline assessment at a one-to-one ratio to either the Exoskeleton group or Usual Care group using an online, third-party, permuted block randomization service (www.randomize.net, Interrand Inc., Ottawa, ON). As such, randomization will remain concealed until group allocation. Randomization will be stratified by site, to control for differences in standard of care (e.g., frequency and duration of physical therapy treatment, length of stay, rehabilitation and admission discharge timing, etc.). Participants will also be stratified by physical function, as baseline functioning is an independent predictor of outcomes such as community mobility and discharge destination [8, 26]. Specifically, participants will be stratified using their baseline Berg Balance Scale score at enrolment, as it has been shown to be correlated with improved walking ability after robot-assisted gait training [27]. A cut-off score of 12 will be used to stratify participants, based on a study [28] which identified a score of 12 at rehabilitation admission to be predictive of regaining unassisted walking after four weeks.

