#### Primary outcome

The primary outcome will be walking ability, measured using the Functional Ambulation Category (FAC) [29]. This is a 6-item scale designed to classify the level of physical support required by subjects in order to walk safely over 10 ft, extending from 1 (unable to walk without the assistance of two people) to 6 (independent walking overground on uneven surfaces and on stairs). It has been shown to have good test-retest reliability and validity in the hemiparetic stroke population [30]. The FAC is also responsive to change within the first four weeks post-stroke and up to six months post-stroke [30]; unlike other walking measures of speed or distance, a value is assigned for the FAC even if the participant is not yet independent in walking.

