#### Sample size estimates

A total of 20 participants will be enrolled in each group (total same *n* = 40). This sample size was calculated using Stata Software (version 11, StataCorp, USA) and assumes a 2-point between-group difference in the Functional Ambulation Category at the end of the intervention [40], setting power at 80% and level of significance at 0.05 (2-sided). This calculation also assumes a standard deviation of 2.0 based on stroke inpatient FAC data from a study by Mehrholz et al. [30]. This between-group difference is realistic, given that participants are 2-person assist (score of 1 on the FAC) on enrolment, and it is expected that those in the Exoskeleton group will make greater improvements in walking ability (independent) compared to those receiving standard care (assistance or supervision required).

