#### Statistical analyses

Descriptive statistics will be used to summarize data. An analysis of covariance (ANCOVA) will be performed to detect post-intervention differences between groups for the primary and secondary measures, using the respective baseline score as the covariate [41]. The significance level will be set at 0.05, and all statistical tests will be two-tailed. Participant data will be analyzed on an intention-to-treat basis, and any missing data will be assessed and analyzed as appropriate using multiple imputation [42]. For measures without a baseline score (i.e., 5-Metre Walk Test, 6-Minute Walk Test), an analysis of variance (ANOVA) will be employed. Confidence intervals (95% CIs) will be reported, where applicable.

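### The primary ANCOVA adjusts only for a nearly constant baseline FAC and leaves out time since stroke onset, which is known for every participant: a cheap, optional gain in precision

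*Protocol article*

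**What the plan says.** All references are to the protocol article.

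- **Participants.** The first inclusion criterion takes patients who "are within 3 months of stroke onset (ischemic infarct or intracerebral hemorrhage"). No other rule on time since onset is stated.
- **Randomization.** Allocation is "at a one-to-one ratio to either the Exoskeleton group or Usual Care group", with two stratifiers. One is site: "Randomization will be stratified by site, to control for differences in standard of care". The other is function: "participants will be stratified using their baseline Berg Balance Scale score at enrolment", split at 12. The cut-off rests on a study that "identified a score of 12 at rehabilitation admission to be predictive of regaining unassisted walking after four weeks".
- **Sample size estimates.** There are 20 patients per group, for a 2-point FAC difference, SD 2.0, 80% power and two-sided 5% significance. The expected difference is justified on the ground that "participants are 2-person assist (score of 1 on the FAC) on enrolment".
- **Statistical analyses.** The primary and secondary measures are compared after the intervention by ANCOVA, "using the respective baseline score as the covariate". No other covariate is named.

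**The concern.** ANCOVA improves on a plain comparison of means only when the covariate varies between patients and predicts the outcome. For the primary outcome the named covariate is baseline FAC. If nearly everyone scores 1, it explains almost nothing and the model reduces in practice to a two-sample t-test. Some spread may remain, because the inclusion criteria also accept patients who need maximal help from one person, but it is small by design.

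Time since onset can range over about three months, is known for every participant, and is a plausible marker of how much recovery lies ahead. Neither the randomisation nor the model uses it. Two things are at stake. Any outcome variance that it explains stays in the error term. And if the arms happen to differ in mean onset time, the planned primary model cannot correct for it, while an adjustment added after the imbalance has been seen would be open to challenge as post hoc.

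**Working it through.** **Inputs from the article:** 20 per arm, difference 2, SD 2.0, two-sided 5%, 80% power (Sample size estimates); entry window of 3 months (Participants).

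**Assumed, because the article gives no figure:** entry times uniform over 0 to 90 days; correlation r between onset time and post-intervention FAC of 0.1 to 0.5, with r = 0 as the null case. Baseline FAC is treated as constant.

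**1. The plan's own figure.** n per arm = 2 × (1.960 + 0.842)² × (2.0/2)² = 15.7, so 16 (normal approximation); the noncentral t needs 17 (80.7% power). The stated 20 follows only with an attrition allowance that the article does not mention (16/0.80 = 20, or 17/0.85 = 20). That is an excess, not a shortfall. Power at 20 per arm by the noncentral t is 86.9%, which is the reference value below.

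**2. Chance imbalance in onset time.** The SD of a uniform over 90 days is 90/√12 = 26.0 days. The SE of the difference in means is 26.0 × √(2/20) = 8.2 days, so the 95% range is ±1.96 × 8.2 = ±16 days, or ±0.62 SD. A difference above 0.5 SD occurs in about 11% of trials.

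**3. Effect on the FAC difference and on power.** The 95% range of the shift is ±1.96 × r × 2.0 × √(2/20). The residual SD after adjustment is 2.0 × √(1 − r²).

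| r | 95% range of shift (points) | Residual SD | Power at 2 points |
|---|---|---|---|
| not adjusted | – | 2.00 | 86.9% |
| 0.1 | ±0.12 | 1.99 | 87.2% |
| 0.3 | ±0.37 | 1.91 | 89.8% |
| 0.5 | ±0.62 | 1.73 | 94.5% |

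For scale, the half-width of the unadjusted 95% confidence interval is 2.024 × 2.0 × √(2/20) = 1.28 points.

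**4. Cost of the extra covariate.** The table's power column counts only the smaller residual SD. Estimating one more coefficient multiplies the variance of the difference by about 1 + 1/36 on average and leaves 37 degrees of freedom. At r = 0 the SE rises from 0.632 to 0.641, the noncentrality falls from 3.16 to 3.12, and power falls from 86.9% to about 86%, a loss just under 1 point. A simulation of 6,000 trials at a 1.8-point difference gave 79.2% without and 78.4% with the covariate at r = 0. A simulation of 20,000 trials at 2 points gave 87.2% without and 88.8% with it at r = 0.3, and 86.7% and 93.5% at r = 0.5. At r = 0.1 the tabled gain of 0.3 points is therefore used up by the cost; the net gain is clear only from about r = 0.3.

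**5. Type I error without adjustment.** In the 20,000-trial simulation it was 5.0% (r = 0.3) and 5.2% (r = 0.5) overall. Among the trials with an imbalance above 0.5 SD it was 8.1% and 13.5%.

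**The case against.** The strongest reply is that nothing here is misstated. ANCOVA on the baseline score is standard, further covariates are often left to an analysis plan, and the same case could be made for age or stroke type. Most of this stands and limits the weight of the point. What remains is that the article does fix the covariate for the primary outcome, and by its own description of the participants that covariate carries little information.

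A reader might infer more than the article supports:

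- **That the estimate is biased or the test invalid.** Randomisation makes imbalance a matter of chance, which the 5% level and the confidence interval already allow for. The raised error rates in step 5 apply only conditionally, in about one trial in nine, and only if r is substantial.
- **That the trial needs the covariate to reach 80% power.** At a 1.8-point difference unadjusted power is about 79%, which could suggest this. The planned difference is 2 points, where it is 86.9%.
- **That recovery stage is wholly uncontrolled at entry.** Stratification by Berg score balances prognosis in part. Stratification by site was chosen with admission and discharge timing partly in mind, and covers differences between sites though not within them.
- **That the Berg cut-off is misapplied because it is scored at enrolment.** Patients are identified from consecutive rehabilitation admissions, and exoskeleton training is meant to start early in the stay. Enrolment is thus intended to be close to admission, and a mismatch with the cut-off study is only inferred.
- **That the article itself says equal scores at different times carry different prognosis.** Its sentence "The FAC is also responsive to change within the first four weeks post-stroke and up to six months post-stroke" describes how the scale measures change. It says nothing about prognosis at a given score.

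The objection that r is unknown also stands. The relevant r is the one that remains after baseline FAC and within site and Berg strata, and it may be smaller than a marginal correlation.

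**Conclusion.** The point holds as a modest improvement to a stated model, not as a flaw in validity. The primary ANCOVA is close to an unadjusted comparison, and it leaves out a prognostic candidate that is available for every participant. Overall type I error and the stated power are sound as planned.

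The size rests on two assumptions that the article cannot settle: the spread of entry times and r. Over the range shown, the 95% range of the shift runs from 6% of the planned effect (0.12/2) to 31% (0.62/2). The power gain runs from nothing, or a loss of just under 1 point, at r near 0 to about 7 points at r = 0.5. Stratification would reduce the imbalance somewhat if onset time differs by site or Berg level.

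That the ANCOVA does not name site and Berg stratum, although both are stratified on, is a separate matter on which this point does not depend.

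**What to change.** In Statistical analyses, pre-specify days from stroke onset to randomisation as an additional continuous covariate in the primary FAC ANCOVA, alongside baseline FAC. Fix this before unblinding; the Trial status section reports recruitment as still ongoing. If the full analysis plan already names this covariate, nothing further is needed.

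Leave eligibility and randomisation unchanged. Three sites by two Berg levels already make 6 strata for 40 patients, so a further stratifier is not an evident improvement.

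The cost is one sentence, one degree of freedom and no new data collection. If onset time turns out to be unrelated to the outcome, the loss is just under 1 percentage point of power.

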#### Randomization

Participants will be randomized by the site coordinator after the baseline assessment at a one-to-one ratio to either the Exoskeleton group or Usual Care group using an online, third-party, permuted block randomization service (www.randomize.net, Interrand Inc., Ottawa, ON). As such, randomization will remain concealed until group allocation. Randomization will be stratified by site, to control for differences in standard of care (e.g., frequency and duration of physical therapy treatment, length of stay, rehabilitation and admission discharge timing, etc.). Participants will also be stratified by physical function, as baseline functioning is an independent predictor of outcomes such as community mobility and discharge destination [8, 26]. Specifically, participants will be stratified using their baseline Berg Balance Scale score at enrolment, as it has been shown to be correlated with improved walking ability after robot-assisted gait training [27]. A cut-off score of 12 will be used to stratify participants, based on a study [28] which identified a score of 12 at rehabilitation admission to be predictive of regaining unassisted walking after four weeks.

#### Exoskeleton device

The EksoGT powered robotic exoskeleton (Ekso Bionics, Richmond, California, USA) will be used to provide the experimental intervention for this study. This exoskeleton has bilateral motor-actuated joints at the hip and knee, as well as a spring-loaded articulation at the ankle to support toe-off and foot clearance during gait via a footplate. The EksoGT is able to power the user’s lower limbs in a walking pattern autonomously (without any active participation by the user), as well as with varied assistance to accommodate any force contribution by the user. The device software allows the therapist to control the degree of assistance, the parameters of gait (step height, step length, swing speed, etc.) and the automaticity of walking (how each step is triggered). These settings can be programmed to tailor the gait training to the individual to ensure active participation that is appropriately challenging. Guidelines for programming the device software to progress gait training with respect to robotic assistance are available in Additional file 1. The device does not provide balance support, and so the user is responsible for maintaining balance and shifting their weight appropriately.

#### Exoskeleton intervention (experimental)

Participants in the Exoskeleton group will have 75% of their standard physical therapy sessions replaced with exoskeleton-based gait rehabilitation. For example, 3 out of 4 weekly physical therapy sessions, or 45 min out of every 60-min session, will be dedicated to the exoskeleton intervention, reserving 25% of therapy time to be dedicated towards other goals. Participants in the Exoskeleton group will wear a powered robotic exoskeleton for their physical therapy sessions beginning after the baseline assessment to allow for repetitious stepping and walking practice from early in their rehabilitation stay. Training will be safely progressed, as tolerated, to reduce the amount of assistance provided by the exoskeleton and to increase the duration of continuous walking bouts. Guidelines for training progression can be seen in Table 1, and specific device programming is available in Additional file 1.

**Table 1 Tab1:** Training progression for experimental group receiving exoskeleton intervention

Timing	Exoskeleton training guidelines
Week 1 (i.e. First 3–4 exoskeleton sessions)	- Require 30 min of upright time in exoskeleton, no set requirement for time in walking (expect approximately 10 min) - Aim for at least 250 steps per session - Familiarize with device, high assistance from therapist and robotics
Week 2 (i.e. 5th session and on)	- Require 15 min of walking time, of 30 min of upright time - Aim for 400 steps per session - Begin reducing assistance from therapist and robotics
Week 3 (i.e. 10th session and on)	- Require 20 min of walking time, of 30 min of upright time - Aim for 550 steps per session - Continue reducing assistance from therapist and robotics
Week 4 and beyond (i.e. beyond 15 sessions)	- Require 25 min of walking time, of 30 min of upright time - Aim for 700+ steps per session - Minimal assistance from therapist and robotics

An algorithm will guide clinicians in deciding when to discontinue daily exoskeleton training (Fig. 2), as it has been found that therapist-guided overground walking practice is equally or more effective than electromechanically-assisted gait for improving walking function once people with stroke are ambulatory [18, 19]. Once a participant reaches a functional threshold wherein they are able to walk for an extended period of time with only minimal assistance, therapists may begin to substitute daily exoskeleton training time to overground gait training. If a therapist chooses to fully discontinue use of the exoskeleton, they will still be required to focus on gait retraining for 75% of their weekly physical therapy time.

